
#### 2.6.2. Psychological Domain

*Anxiety and stress.* Symptoms were quantified using the Generalized Anxiety Disorder 7-item (GAD-7) scale, a validated tool that measures the severity of generalized anxiety across several dimensions including nervousness, worry, and restlessness. This scale rates symptoms from 0 (“not at all”) to 3 (“nearly every day”), with total scores ranging from 0 to 21 [67].

*Emotional states* were assessed using the validate Positive and Negative Affect Scale (PANAS) [68,69,70]. The scale consists of two subscales, each composed of 10 items. The Positive Affect subscale measures feelings associated with activation and pleasure, with higher scores (ranging from 10 to 50) indicating a greater positive affect. The Negative Affect subscale captures emotions linked to distress and discomfort, where higher scores indicate a greater negative affect. Participants rated the extent to which they had experienced each adjective over the past few weeks.

*Interoceptive awareness.* Interoceptive awareness was evaluated using the Multidimensional Assessment of Interoceptive Awareness (MAIA), which consists of 32 items spanning various dimensions of interoception. These dimensions include the ability to notice subtle bodily sensations, not being distracted or distressed by them, regulating attention to the body’s signals, and developing emotional awareness related to these sensations. Participants rated each item on a scale from 0 (never) to 5 (always), with higher scores indicating greater interoceptive awareness and better regulation of bodily signals [71].

*Well-being and quality of life.* Well-being was evaluated using two validated instruments. Ryff’s Psychological Well-Being Scale assesses key facets of psychological functioning such as self-acceptance and personal growth through 39 items. Total scores ranged from 39 to 234; higher scores indicate greater psychological well-being [72,73]. Additionally, health-related quality of life was assessed using the validated Spanish version of the 36-item Short-Form Health Survey (SF-36). The SF-36 measures eight dimensions: physical functioning, role limitations due to physical health, bodily pain, general health, vitality, social functioning, role limitations due to emotional problems, and mental health. Scores for each dimension range from 0 to 100, with higher scores indicating better health-related quality of life [74].

#### 2.6.3. Control Variables

Different variables are recorded that may influence the study results even though they are not part of the intervention: sex, age, educational level, marital status, occupational status, and income level; personal history of depression (depression duration) and medication use; information on the presence of comorbidities; sleep time and quality (accelerometer); adherence to a Mediterranean diet, measured using the PREDIMED questionnaire [75,76]; and usual intake estimates of food groups, energy, and nutrients using a self-administered semi-quantitative food-frequency questionnaire (FFQ) [77] and 5-day recalls [78].

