The SONRIE study (ClinicalTrials.gov Identifier: NCT05849792), originally launched in September 2019, is RCT designed to explore the effects of a 12-week online intervention combining iCBT and structured physical exercise in adults diagnosed with mild-to-moderate depression. Although initiated before the global outbreak of COVID-19, subsequent confinement periods have underscored the study’s relevance and applicability in scenarios of isolation. The primary aim of the SONRIE study was to evaluate the immediate and sustained effects of this combined online intervention on depressive symptoms. Additionally, the study has defined secondary objectives: (i) to examine the effects of the intervention on physical health parameters such as body composition, physical fitness, and blood biomarkers including plasma levels of eCBs (AEA and 2-AG) and their analogs or BDNF levels; (ii) to explore its influence on psychological dimensions such as anxiety, stress, emotional states, interoceptive awareness, and overall well-being; (iii) to investigate interrelationships among lifestyle factors including physical activity, sedentary behavior, sleep patterns, and dietary habits, and their predictive value on depressive outcomes; and (iv) to assess the sustainability of the intervention effects during an 8-week follow-up period without further treatment. We hypothesize that participants in the combined intervention group will experience significantly greater reductions in depressive symptoms compared to participants receiving usual care. Secondary hypotheses propose that improvements in depressive symptoms may be associated with positive changes in plasma levels of eCBs and their analogs, and BDNF signaling, alongside improved physical fitness, sleep quality, and emotional regulation. By clearly delineating primary and secondary outcomes, the SONRIE study aims to provide robust evidence on the clinical efficacy and biological underpinnings of an integrated, internet-based psycho-physical exercise intervention program for depression.

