### 2.3. Sample Size and Randomization

To detect a minimum mean difference of 8.26 in the primary outcome (depression symptoms), with an assumed standard deviation of 9.36, a sample size of 50 participants (25 per group) was calculated. These assumptions were based on the results of Stelzer et al. [38], who conducted an RCT involving individuals with depression undergoing a structured physical exercise psychotherapy intervention. Although their intervention modality was not delivered online, the target population and outcome measure were comparable to those used in the present study. The observed change in depressive symptoms in that trial was considered clinically meaningful and therefore appropriate to inform the sample size estimation in the context of exercise-based interventions for depression. This calculation assumed an alpha error of 0.05 and a statistical power of 85%. To accommodate potential loss to follow-up, 80 participants were initially recruited, accounting for a possible dropout rate. This ensures sufficient statistical power for the SONRIE study throughout its duration.

Participants were randomized in a 1:1 ratio to either the Experimental Group (EG; n = 40) or Control Group (CG; n = 40), ensuring balance in sex, age, and clinical severity of depression. The randomization process was conducted using a computer-generated sequence through STATA version 16.0 (Stata Corp, College Station, TX, USA). To prevent selection bias, allocation concealment was ensured by using a centralized randomization procedure, where the sequence was generated and stored by an independent researcher not involved in recruitment, intervention, or data collection. Group assignments were only revealed to participants after baseline assessments were completed, ensuring that neither researchers nor participants could predict or influence the allocation process.

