### 2.8. Statistical Analysis

To assess the effectiveness of randomization, baseline (pre-test) values will be compared between the EG and the CG for potential clinically important differences using independent samples *t*-tests for continuous variables and chi-square tests for categorical variables. Effect sizes will be calculated to quantify the magnitude of any differences observed. The difference between groups in the change (pre, post, and 8-week follow-up) of the primary outcome (e.g., depression scores) and all secondary outcomes will be analyzed using Analysis of Covariance (ANCOVA) for continuous outcomes that meet model assumptions. For outcomes that are not continuous or do not meet ANCOVA assumptions, appropriate generalized linear models will be used, specifying the distribution and link function according to the nature of the data (e.g., logistic regression for binary outcomes). The change score will be the dependent variable, with group (EG or CG), time points (e.g., post-intervention, follow-up), and their interaction included as fixed effects. Baseline values and relevant confounding variables (e.g., age, sex) will be included as covariates to adjust for initial differences and control for potential confounders. Model assumptions (e.g., normality, homogeneity of variances, linearity) will be assessed using diagnostic plots and statistical tests. In cases where assumptions are violated, data transformations or non-parametric alternatives will be considered. Effect sizes (with 95% confidence intervals) and statistical significance will be reported for the effects of group (between-subjects), time (within-subject), and the group × time interaction. Partial eta squared (ηp^2^) will be reported for ANCOVA, with effect sizes interpreted as small (ηp^2^ ≥ 0.01), medium (ηp^2^ ≥ 0.06), and large (ηp^2^ ≥ 0.14) according to Cohen’s guidelines [84,85]. Statistical significance will be set at *p* < 0.05. To address the issue of multiple comparisons, *p*-values will be adjusted using the Bonferroni correction [86]. The primary analysis will follow a per-protocol approach, including only participants who attended at least 80% of the intervention sessions. Missing data will be handled using an intention-to-treat (ITT) approach, ensuring that all randomized participants are included in the analysis. A dropout analysis will be conducted to determine whether participants who withdraw differ significantly from those who complete the study. Additionally, sensitivity analyses will be performed to confirm the robustness of the results under various assumptions about missing data. As high attrition is common in internet-based interventions for depression [39,40], these strategies are essential to reduce the risk of attrition bias and preserve internal validity [87]. All statistical analyses will be performed using STATA version 16.0 (StataCorp LP, College Station, TX, USA).

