**Control Variables**	
Sociodemographic and Medical History Information	- Self-reported questionnaire
Sleep Time and Quality	- ActiGraph GT3X Accelerometer
Dietary Habits	- 5-day Dietary Recalls - PREDIMED Questionnaire - Food Frequency Questionnaire (FFQ)

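### Sleep quality is hypothesised to improve but is classified as a control variable, so it has no planned between-group comparison and sits among the candidate confounders

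*Protocol article*

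**What the plan says.** **Sleep as an expected effect.** The secondary hypotheses in the Introduction link improvement in depressive symptoms to biomarker changes, "alongside improved physical fitness, sleep quality, and emotional regulation". Objective (iii) in the same section also treats sleep as a predictor, listing "sleep patterns, and dietary habits, and their predictive value on depressive outcomes".

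**Sleep as a control variable.** Section 2.6.3 opens: "Different variables are recorded that may influence the study results even though they are not part of the intervention". Its list includes "sleep time and quality (accelerometer); adherence to a Mediterranean diet". Table 1 puts "Sleep Time and Quality" in the Control Variables block, below the physical and psychological outcome domains. Sections 2.6.1 and 2.6.2 do not list sleep.

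**The model.** Section 2.8 applies ANCOVA, or a generalised linear model, to the primary outcome and the secondary outcomes. On adjustment it says: "Baseline values and relevant confounding variables (e.g., age, sex) will be included as covariates". The stated purpose is to deal with initial differences and potential confounding.

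**Randomisation and its check.** Section 2.3 describes 1:1 allocation, "ensuring balance in sex, age, and clinical severity of depression". Section 2.8 begins: "To assess the effectiveness of randomization, baseline (pre-test) values will be compared between the EG and the CG", using t-tests and chi-square tests, with effect sizes reported as well.

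**The concern.** A variable that the intervention is expected to change is an outcome. A variable that influences the result from outside the intervention is a control variable. The article gives sleep both roles, and the choice decides what happens to it in the analysis.

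As a secondary outcome, sleep would get an adjusted between-group comparison with a confidence interval. As a control variable it gets none, and it becomes eligible for the right-hand side of the BDI model. At stake is the trial's ability to answer a question it poses itself. A lesser matter is that the covariate sentence sets no time point for the confounders, so nothing written there excludes a sleep value measured after treatment began.

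Two smaller points sit in the same paragraphs. Clinical severity was balanced at randomisation but is not named among the covariates. Baseline significance tests are given a task that they cannot perform.

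**Working it through.** **1. Sleep's role, section by section**

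| Place | Role given to sleep |
|---|---|
| Introduction, secondary hypotheses | Expected to improve |
| Introduction, objective (iii) | Predictor of depressive outcomes |
| Sections 2.6.1 and 2.6.2 | Not listed |
| Section 2.6.3 and Table 1 | Control variable |
| Section 2.8 | Not named; the comparison covers primary and secondary outcomes |

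Physical fitness appears in the same hypothesis as sleep quality and is a secondary outcome in Section 2.6.1. Physical activity and sedentary time appear in objective (iii) with sleep and come from the same accelerometer; they too are secondary outcomes. Sleep is treated differently without a stated reason. Read together, Sections 2.6 and 2.8 give it no between-group comparison.

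**2. Does the time point of a sleep covariate matter?**

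The scale comes from Section 2.3: difference 8.26, SD 9.36, alpha 0.05, power 85%, 25 per group. That sample size reproduces with a two-sided test. The normal approximation gives 2 × (1.960 + 1.036)² × (9.36/8.26)² = 23.06, so 24 per group. The t-test version gives 24.06, so 25 per group.

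If sleep measured after randomisation were a covariate, the part of the BDI effect that runs through sleep would be removed:

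removed points = (effect on sleep, in SD) × (fall in BDI, in SD, per SD of sleep) × 9.36

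The documents give neither of the first two terms. Both are assumed here to lie between 0.2 and 0.5.

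- Low end: 0.2 × 0.2 × 9.36 = 0.37 points; 0.37/8.26 = 4.5% of the planned effect.
- High end: 0.5 × 0.5 × 9.36 = 2.34 points; 2.34/8.26 = 28%.

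A large simulation (400,000 records, sleep effect 0.5 SD, slope 0.3) gave these BDI effects:

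| Covariates | Effect (points) |
|---|---|
| Baseline BDI | 8.28 |
| Baseline BDI and baseline sleep | 8.28 |
| Baseline BDI and post-treatment sleep | 6.88 |

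The loss of 1.40 points agrees with 0.5 × 0.3 × 9.36 = 1.40. Baseline sleep does no harm; only the later value does. This supports a baseline-only rule. It does not describe an analysis that the article plans.

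**3. Clinical severity**

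Section 2.5 describes the BDI as a measure of depression severity, and Section 2.8 puts baseline values in the model. The primary model therefore already carries a severity score. In the same simulation, adding a severity category to baseline BDI left the effect at 8.28. The unnamed factor matters mainly for secondary outcomes such as fitness or blood markers, whose baseline value is not a depression score. There, leaving out a balanced factor costs precision and can make standard errors too large. It does not bias the effect.

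**4. Baseline tests**

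Under sound random allocation every baseline difference arises by chance, so a p-value tests a hypothesis already known to be true. It cannot show whether randomisation was effective. The effect sizes in the same paragraph are the useful part.

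**The case against.** The strongest reply has four parts.

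- **The hypothesis is tentative.** It speaks of possible associations with symptom improvement, and objective (iii) examines sleep as a predictor, so sleep is not ignored. This stands in part. It would be too strong to say that sleep goes unexamined. The hypothesis still presupposes that sleep improves, and only a between-group comparison can attribute that to the intervention.
- **Over-adjustment is not in the text.** A reader might infer that the ANCOVA will adjust away part of the BDI effect. The documents do not support that. Section 2.6.3 says that control variables are recorded, not modelled; no section puts a later sleep value in the model; and the stated aim of dealing with initial differences points to baseline values.
- **Severity is not dropped from the primary model.** The named covariates are examples, and baseline BDI is included. This stands. A reader might also infer that omitting a balancing factor adjusts the effect away; it cannot.
- **A condensed article need not close its covariate list.** This stands too, and the open list alone is no finding. What remains is that the article twice places sleep in a class that conflicts with its own hypothesis.

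On the baseline tests, the article also looks for clinically important differences and nowhere says that covariates are chosen by p-value. The criticism is confined to the purpose stated for the tests.

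**Conclusion.** The inconsistency is real and rests on the text alone. Sleep quality is expected to improve, is classified as a control variable in two places, and so has no planned between-group comparison. Its size is one hypothesised effect without a test.

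No bias or power loss in the primary analysis follows from the documents. The 0.37 to 2.34 points above depend on assumed links between treatment, sleep and BDI, and on a post-treatment sleep covariate that the article does not specify. A reader might turn that range into a loss of power. Such a figure would rest on an assumed mediated share and an SD held fixed although the covariate would explain some variance, and it would describe no planned analysis.

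The severity factor is a small gain in precision, mainly for secondary outcomes. The baseline-test wording is a minor correction.

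**What to change.** - **Sections 2.6 and 2.6.3, Table 1:** move accelerometer sleep time and quality to the secondary outcomes. Alternatively, take sleep quality out of the secondary hypotheses and keep it as a baseline descriptor and predictor.
- **Section 2.8, covariates:** state that all covariates are measured at baseline, so that nothing the intervention is expected to change is adjusted for after randomisation. Name the baseline value of the outcome, age, sex and the clinical severity factor used in randomisation.
- **Section 2.8, baseline comparison:** give a descriptive table with effect sizes and drop the significance tests of randomisation.

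**Cost.** These are wording changes, and Section 2.8 is written in the future tense. Moving sleep adds one outcome to the Bonferroni family, or two if time and quality are tested separately. Section 2.6.1 already describes 24-hour accelerometer wear, so later sleep data are likely to exist. However, Section 2.4 schedules only primary and secondary outcomes at the three time points and Section 2.6.3 gives no schedule, so availability should be confirmed. Because data collection has ended, the change should be dated and should say whether any sleep results had been seen.

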### 2.7. Internet-Based Psycho-Physical Exercise Intervention Program

#### 2.7.1. Control Group (CG, Usual Care)

Participants randomly assigned to the CG received standard care throughout the study. This group did not engage in the internet-based psycho-physical exercise intervention program but continued their usual care routines.

#### 2.7.2. Experimental Group (EG, Enhanced Care with Physical Exercise and iCBT)

The psycho-physical exercise intervention implemented in this study refers to a structured and coordinated program that integrates a multicomponent physical exercise protocol with iCBT. Delivered entirely online, this dual approach was designed to address both the physiological and psychological dimensions of depression. The physical exercise component included balance, resistance, and CRF training, individually tailored and progressive, while the iCBT program was based on the Unified Protocol and targeted emotional regulation, cognitive restructuring, and behavioral activation. Both components were scheduled in a complementary manner, with participants viewing the psychological modules prior to each supervised exercise session, thereby enhancing the integrative therapeutic effect of the intervention.

The exercise protocol followed the Consensus on Exercise Reporting Template (CERT) for transparency and replicability [79]. Sessions were conducted by a Physical Educator and Sports Sciences Specialist registered according to Spanish law and holding a Master’s degree in Physical Activity and Health, with initial support provided by a physical therapist. This 12-week exercise program consisted of three weekly sessions: one supervised online session each Tuesday and two asynchronous unsupervised sessions. Sessions were delivered through private YouTube videos, accessible only to study participants, thereby maintaining confidentiality while providing on-demand exercise guidance. Exercise intensity was individually prescribed using the Borg Rate of Perceived Exertion (RPE) scale, targeting moderate to vigorous intensity as recommended by the American College of Sports Medicine’s (ACSM) [80]. Exercise volume adhered to the World Health Organization’s 2020 physical activity guidelines for adults [80].

Each 60–90 min session began with a 7–10 min warm-up involving dynamic stretches (e.g., arm circles, leg swings) and mobility exercises (e.g., hip rotations, ankle rolls) to gradually increase heart rate and prepare the body for physical activity. The main segment comprised balance, resistance, and CRF training. Balance training lasted 10 min per session, designed to improve coordination, postural control, and core stability. Participants progressed from static balance exercise to dynamic and advanced coordination tasks, maintaining a low perceived intensity (RPE 1–3). Resistance training occupied 25–35 min per session, emphasizing the progressive enhancement of muscular strength, motor control, and core stability. Exercises included squats, lateral and frontal lunges, biceps curls, push-ups, bent-over rows, and shoulder presses structured into 3–4 sets (8–12 repetitions or duration-based sets), following ACSM guidelines [81]. Progression involved increasing time under tension (TUT) principles (from week 4 onwards) and introducing light-to-moderate external weights [82]. The training intensity progressively increased from RPE 3–4 initially to RPE 7–8 by week 12. The CRF training, lasting 13–14 min, included aerobic exercises such as dance aerobics and step routines. Sessions were structured into 2–3 segments of 2 to 9 min each with brief rest intervals (45–60 s). The training intensity started at RPE 3–4 and gradually increased to RPE 7–8 by week 12, designed to achieve 55–89% of the participant’s heart rate reserve, consistent with ACSM recommendations [81]. The sessions concluded with an 8-10 min cool-down period incorporating stretching for major muscle groups, relaxation techniques, and postural adjustments. Participants completed pre- and post-session Google Forms questionnaires for supervised and unsupervised sessions to track attendance and monitor participant safety by collecting information on perceived exertion and satisfaction. The supervising specialist reviewed these responses regularly to detect signs of excessive fatigue, discomfort, injury, or dissatisfaction, and provided personalized support or adjustments to the program as needed. In addition, weekly adherence to the prescribed exercise sessions was monitored by analyzing these logs. Participants who missed sessions or reported difficulties received immediate individualized follow-up from the supervising fitness specialist to ensure ongoing engagement. Successful adherence was defined as completion of at least 80% of planned sessions. (Detailed session structure and progression are available in Table A1).

The psychological protocol of the intervention consisted of the iCBT program, adapted from a face-to-face Unified Protocol for the transdiagnostic treatment of emotional disorders [83]. It was conducted by a psychologist registered in accordance with Spanish law, holding a Master’s degree in Sports Psychology, a Master’s degree in Neuropsychology, and a specific qualification in the Unified Protocol. Ethical considerations were strictly adhered to throughout the intervention. The iCBT program comprised 18 modules addressing four main dimensions: physiological, emotional, behavioral, and cognitive aspects (Table A2). Modules included asynchronous, video-guided sessions lasting approximately 30 min each, delivered individually prior to the supervised exercise session. Following an introductory first session, participants received two sessions per week from weeks 2 to 7, and one session per week from weeks 8 to 12. Each module sequentially built upon the previous one, ensuring a cohesive and progressive learning experience. The content of the iCBT modules integrated psycho-educational components on cognitive skills (e.g., identifying and modifying negative thoughts and emotions), behavioral techniques (e.g., behavioral activation, posture modification), emotional regulation strategies (bottom-up and top-down approaches), coping skills (problem-solving and reducing avoidance behaviors), and insights into neurochemical regulation of mood (serotonin, dopamine, endorphins, and oxytocin). Participants received practical exercises and interactive tasks in each module, facilitating skill implementation and practice. Participants completed the PANAS before and after each supervised exercise session. As iCBT modules were scheduled to be viewed immediately before these sessions, PANAS scores also served to assess emotional responses to the psychological component of the intervention. These data, along with weekly feedback forms, were reviewed by the supervising psychologist to monitor adherence and detect signs of emotional distress or disengagement. Participants were encouraged to report any psychological discomfort, and the psychologist remained available throughout the program to provide support or intervention adjustments as needed. Successful adherence to the iCBT component was defined as completion of at least 80% of the modules.

